## Abstract

**Background:**

Osteochondral talar defects usually affect athletic patients. The primary surgical treatment consists of arthroscopic debridement and microfracturing. Although this is mostly successful, early sport resumption is difficult to achieve, and it can take up to one year to obtain clinical improvement. Pulsed electromagnetic fields (PEMFs) may be effective for talar defects after arthroscopic treatment by promoting tissue healing, suppressing inflammation, and relieving pain. We hypothesize that PEMF-treatment compared to sham-treatment after arthroscopy will lead to earlier resumption of sports, and aim at 25% increase in patients that resume sports.

**Methods/Design:**

A prospective, double-blind, randomized, placebo-controlled trial (RCT) will be conducted in five centers throughout the Netherlands and Belgium. 68 patients will be randomized to either active PEMF-treatment or sham-treatment for 60 days, four hours daily. They will be followed-up for one year. The combined primary outcome measures are (a) the percentage of patients that resume and maintain sports, and (b) the time to resumption of sports, defined by the Ankle Activity Score. Secondary outcome measures include resumption of work, subjective and objective scoring systems (American Orthopaedic Foot and Ankle Society – Ankle-Hindfoot Scale, Foot Ankle Outcome Score, Numeric Rating Scales of pain and satisfaction, EuroQol-5D), and computed tomography. Time to resumption of sports will be analyzed using Kaplan-Meier curves and log-rank tests.

**Discussion:**

This trial will provide level-1 evidence on the effectiveness of PEMFs in the management of osteochondral ankle lesions after arthroscopy.

**Trial registration:**

Netherlands Trial Register (NTR1636)

## Background

Osteochondral defects (ODs) of the talus often have a severe impact on the quality of life of the patients. The patients are usually young and athletic; most are male (62%) in the third decade of their lives after a traumatic ankle sprain [1]. The primary treatment of a symptomatic OD consists of arthroscopic debridement and microfracturing [2]. This treatment yields 87% good or excellent results [3]. However, it can take up to one year to obtain improvement of clinical symptoms. Moreover, it is a great challenge to achieve early resumption of sports, which is the main goal of many of these young patients. In a series published in 2007, 26 "high-demand" athletic patients with an OD returned to sports at a mean of 15 weeks after debridement and microfracturing [4]. If we could shorten this period, we would considerably improve the quality of life in these active patients.

A potential solution to obtain this goal is the application of pulsed electromagnetic fields (PEMFs). Bassett in the 1960s and 1970s introduced and improved the clinical use of this treatment modality [5,6]. Since then, PEMFs have been applied increasingly, including their use in the treatment of osteoarthritis and (non-united) fractures [7,8]. They are designed as a portable PEMF generator, which consists of electromagnetic fields with an on-off effect of pulsing. This produces athermal effects that suppress inflammation, promote tissue healing, and relieve pain [9]. In vitro and in vivo studies have shown that PEMFs act as adenosine A2a agonists, leading to an increase of Transforming Growth Factor β-1, thereby improving bone development, reducing cartilage damage and increasing chondrocyte proliferation [10-21]. These results clearly indicate improved regeneration of bone and possibly cartilage in a scientific setting.

Clinically, its favorable effects are less obvious. PEMF as a solitary treatment for osteoarthritis of the knee has been repeatedly investigated, with conflicting results [7,22-25]. Although the effect of PEMFs on osteoarthritis of the knee seems equivocal, their value in the additional treatment of other bony and cartilaginous pathologies is promising. PEMFs have been proven as a successful method in fracture healing, especially in the case of non-union [8,26,27]. PEMF-treatment also favors the recovery of patients after arthroscopic treatment of chondral lesions in the knee, and reduces the use of non-steroidal anti-inflammatory drugs [28]. To our knowledge, sport resumption with the use of PEMFs has not been investigated. Based on the above data, we believe that PEMFs may act on ODs by improving bone regeneration and suppressing inflammation evoked by surgery.

When the above results are combined, it seems justified to state that additional PEMF-treatment may contribute to the management of ODs. Our study question is: "Does treatment with PEMFs compared to sham device lead to earlier resumption of sports in a higher percentage of patients with an osteochondral defect of the talus after arthroscopic debridement and microfracturing?".

## Methods/Design

### Study design and informed consent

The study is designed as a double-blind, randomized, placebo controlled, multicenter trial, which is in accordance with the Declaration of Helsinki [29]. The methodology will follow CONSORT (Consolidation of Standards of Reporting Trials) guidelines [30,31]. Five centers in the Netherlands and Belgium will participate. Approval has been obtained from the local Medical Ethics Committees in the participating centers (MEC 08/236). Written informed consent for participation in the study will be obtained from all patients at study entry. An information letter notifying the patients' participation will be sent to their general practitioners.

### Inclusion criteria

• Patients with a symptomatic OD of the talus who are scheduled for arthroscopic debridement and microfracture [2]

• OD diameter < 15 mm on CT (in three dimensions: medial-lateral, anterior-posterior and superior-inferior)

• Ankle Activity Score (AAS) ≥ 4 before symptoms (Table 1) [35]

**Table 1 T1:** Ankle Activity Score by Halasi et al. [35]

		Ankle Activity Score^a^		
Category	Sports and Activities	T	C	R

10	American football	10	9	8
	Basketball	10	9	8
	Gymnastics	10	9	8
	Handball	10	9	8
	Rugby	10	9	8
	Soccer	10	9	8
9	Hockey	9	8	7
	Korfball	9	8	7
	Martial arts: judo, karate, kung fu, taekwondo	9	8	7
	Orienteering	9	8	7
	Rhythmic gymnastics	9	8	7
	Volleyball	9	8	7
8	Boxing	8	7	6
	Freestyle snowboarding	8	7	6
	Ice hockey	8	7	6
	Tennis	8	7	6
	Wrestling	8	7	6
7	Aerobics, fitness	7	6	5
	Badminton	7	6	5
	Baseball	7	6	5
	Cross-country running (running on uneven ground)	7	6	5
	Modern pentathlon	7	6	5
	Squash	7	6	5
	Surfing, windsurfing	7	6	5
	Table tennis	7	6	5
	Track and field: field events	7	6	5
	Water skiing	7	6	5
6	Dancing	6	5	4
	Fencing	6	5	4
	Floorball	6	5	4
	Mountain and hill climbing	6	5	4
	Nordic skiing	6	5	4
	Parachuting	6	5	4
	Softball	6	5	4
	Special professions and working activities^b^	6		
5	Diving	5	5	4
	Scuba diving	5	5	4
	Skating, in-line skating	5	5	4
	Track and field: track events (running on even ground)	5	5	4
	Triathlon	5	5	4
	Weightlifting, body building	5	5	4
	All competitive sports of categories 4 and 3 with seasonal conditioning	5		
	Heavy physical work	5		
4	Alpine skiing and snowboarding	4	4	4
	Bowling/curling	4	4	4
	Golf	4	4	4
	Mountain biking/bmx	4	4	4
	Power lifting	4	4	4
	Sailing	4	4	4
	Physical work	4		
3	Cycling	3	3	3
	Equestrian	3	3	3
	Motorsports, technical sports	3	3	3
	Rowing, kayaking	3	3	3
	Shooting, archery	3	3	3
	Water polo and swimming	3	3	3
	Able to walk on any uneven ground	3		
2	No sports, everyday activities not limited	2		
1	Able to walk on even ground, but everyday activities limited	1		
0	Unable to walk, disabled because of ankle problems	0		

^a^T, top level (international elite, professional, national team, or first division); C, lower competitive levels; R, recreational level (participation should be considered only if it exceeds 50 hours per year).

^b^Special professions include ballet dancer, professional soldier, special rescue worker, stuntperson, and so forth.

If multiple options are applicable, the highest level is chosen.

• Age 18 years or older

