### Standard treatment and investigational treatment

All surgical procedures will be performed using a standardized technique [2]. Briefly, the ankle joint is approached by arthroscopy using an anterior or posterior approach. The OD is identified with a probe and debrided with a curette and bonecutter shaver. All unstable bone and cartilage are removed. After full debridement, the subchondral bone is perforated with a microfracture awl, with intervals of approximately 3 mm. At the end of the procedure a pressure bandage is applied.

After surgery the protocol-based rehabilitation program, guided by a physiotherapist, will be equal in both groups. It will be initiated with partial (eggshell) weight bearing on crutches, as tolerated, and progressed to full weight bearing over a period of six weeks. During this period active non-weight-bearing and partial weight-bearing sagittal range of motion exercises are encouraged, i.e., 15 minutes twice daily. After this six week' period, resumption of sports will be permitted as tolerated, and will not be directed by the clinician.

In both groups the investigational treatment (active PEMF-treatment or sham device treatment) will start within three days after surgery. It will be applied four hours daily (in one or two sessions) for a period of 60 days [37,38]. The patients' compliance will be monitored by a clock inside the device that records the hours of stimulation.

The prescription of nonsteroidal anti-inflammatory drugs will be avoided due to their negative effect on bone regeneration [39]. The use of paracetamol will be allowed up to a maximum dose of 4 g/d and will be discontinued one week before the visits at baseline, 1 month, 2 months, 6 months and 1 year.

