### Definitions

#### Primary outcome measures

Because there is no consensus as to defining what actual resumption of sport is – as Saxena and Eakin stated [4] – we define time to resumption of sports as the time after arthroscopy (weeks) until initiation of any sport with a minimum level of the pre-symptoms level minus 1 point on AAS, and maintained for at least 30 days. If a patient's activity level decreases to below the minimum level within 30 days after sport resumption, the resumption date will not be counted. To evaluate the level of sport activity, we will use the AAS that has been developed and validated by Halasi and associates [35]. This 10-point score is based on the type and level of sport or work, with 0 points indicating the lowest activity and 10 points indicating the highest activity (Table 1).

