### Data acquisition and follow-up

Participating patients will be assessed at the following time points (Table 2):

**Table 2 T2:** Patient assessment.

	Physician									Patient			
	
	Baseline characteristics*	Sport resumption	Work resumption	AAS	AOFAS-AHS	CT	Wound inspection	Compliance	Adverse events	FAOS	EQ-5D	NRS pain	NRS satisfaction
**Preoperative**	X			X	X	X				X	X	X	

**1–2 weeks**							X	X	X				

**1 month**			X					X	X		X	X	X

**2 months**		X	X	X	X		X	X	X	X	X	X	X

**6 months**		X	X	X							X	X	

**1 year**		X	X	X	X	X			X	X	X	X	X

* Baseline characteristics include age, gender, weight, height, affected side, duration of symptoms, type of sport and profession, past medical history, smoking status, and size, localization and classification of osteochondral defect on computed tomography.

AAS = Ankle Activity Score; AOFAS-AHS = American Orthopaedic Foot and Ankle Society – Ankle-Hindfoot Scale; CT = Computed Tomography; FAOS = Foot and Ankle Outcome Score; EQ-5D = EuroQol questionnaire; NRS = Numeric Rating Scale.

1. *Preoperatively*: information letter, informed consent, baseline characteristics (age, gender, weight, height, affected side, duration of symptoms, past medical history, smoking status), type of sport and profession, AAS (2×: before symptoms and at preoperative assessment), AOFAS-AHS, FAOS, EQ-5D, NRS pain (2×: at rest and when running), CT: size, localization and classification of the OD (Table 3) [52]

**Table 3 T3:** Computed tomography classification of osteochondral defects of the talus [52].

Grade	Description
I	Compression
II	Partially fractured but undisplaced
III	Completely fractured but undisplaced
IV	Displaced fracture
V	Radiolucent (fibrous) defect

2. *1–2 weeks postoperatively*: check compliance, (S)AEs, wound inspection (healing, signs of infection)

3. *1 month postoperatively*: check compliance, (S)AEs, resumption of work, EQ-5D, NRS pain (at rest) and satisfaction

4. *2 months postoperatively*: check compliance, (S)AEs, resumption of sport and work, AAS, AOFAS-AHS, FAOS, EQ-5D, NRS pain (at rest and when running, if applicable) and satisfaction, wound inspection, stop PEMF- or sham-treatment

5. *6 months postoperatively*: resumption and maintenance of sport and work, AAS, EQ-5D, NRS pain (at rest and when running)

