### Statistical methods

The following baseline characteristics will be summarized using descriptive statistics: number of patients, gender, age, affected side, duration of symptoms (months), prior ankle surgery, body mass index (kg/m^2^), trauma, smoking, size of lesion (mm), classification, duration of PEMF- or sham-treatment (hours), AAS, NRS pain, FAOS, AOFAS-AHS, and EQ-5D. Continuous data will be presented as mean and standard deviation if normally distributed, or as median and range in case of skewed distribution.

The main analysis of this trial consists of a comparison between the treatment groups of the primary outcomes: number of patients who resume and maintain sports and the time to resumption of sport (of the patients who resume sport). The number of patients who resume sport will be analyzed using the two group *X*^2 ^test, whereas the difference in mean weeks to sport resumption will be analyzed by a two group Student's *t*-test. Both *p*-values will be combined using the Fisher's combination test. Kaplan-Meier survival curves and the log-rank test will also be used for comparing time to resumption of sport. The stratification variables will be included in the primary analysis.

The repeated datastructure of the secondary outcomes (AAS, AOFAS-AHS, FAOS, EQ-5D, NRS-pain, and NRS-satisfaction) will be analyzed with linear mixed models, including a time-treatment interaction effect. The number of adverse events and time to resumption of work will be analyzed using a *Χ*^2 ^test or log-rank test, when appropriate. Analyses will be based on the intention-to-treat principle and performed in SPSS. Statistical uncertainty will be quantified via 95% confidence intervals.

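### The preoperative drop in AAS is measured and probably predicts both primary outcomes, but it is neither stratified for nor named in the primary analysis

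*Protocol article*

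**What the plan says.** Under Inclusion criteria, the disease condition is "Patients with a symptomatic OD of the talus who are scheduled for arthroscopic debridement and microfracture" and the activity condition is "Ankle Activity Score (AAS) ≥ 4 before symptoms". No inclusion or exclusion criterion refers to the activity level at the time of surgery.

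Under Primary outcome measures, time runs from arthroscopy "until initiation of any sport with a minimum level of the pre-symptoms level minus 1 point on AAS, and maintained for at least 30 days". The target is therefore set by the pre-symptoms score alone.

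Under Data acquisition and follow-up, the preoperative visit records "AAS (2×: before symptoms and at preoperative assessment", so the drop from one to the other is known for every patient before randomised treatment starts.

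Under Randomization, the stratification factors are center, body mass index and defect diameter. Under Statistical methods, AAS appears in the baseline summary and as a repeated secondary outcome. For the primary comparison the only covariate statement is "The stratification variables will be included in the primary analysis".

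**The concern.** The entry rule admits two quite different kinds of patient. One has a painful defect but still plays at, or one point below, the old level. The other has given up sport and scores perhaps 2. Both are judged after surgery against the pre-symptoms level minus 1. The first returns to something done until the operation; the second must regain something lost for months or longer. It is reasonable to expect the first to resume more often and sooner, whatever the arm.

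Two things could follow. If the first group is sizeable and treatment changes little for them, the difference between arms shrinks. Whatever the treatment effect in them, a strong baseline predictor left out of the analysis of a 68-patient trial costs precision and leaves a chance imbalance uncorrected.

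**Working it through.** **Can such patients enter?** Table 1 of the article shows that they can.
- Recreational tennis scores 6, so the endpoint level is 6 − 1 = 5. A patient who plays on with pain is still at 6. One who has moved to a recreational category 7 sport, such as badminton, is at 5. Both are already at the endpoint level before surgery.
- At the entry threshold, a pre-symptoms AAS of 4 (golf, for example) gives an endpoint level of 3, which recreational cycling or swimming meets.

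**Have they met the endpoint at entry?** No. Time is counted from arthroscopy, all patients go through a six-week weight-bearing progression, and only then does the plan say "After this six week' period, resumption of sports will be permitted as tolerated, and will not be directed by the clinician". Each must return and hold the level for 30 days.

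**The plan's own power.** Inputs from Sample size: 30 per arm, resumption 0.50 v 0.75, time among resumers 15 v 12 weeks with SD 4, two-sided 0.05. The test statistic is −2 ln(p₁p₂), where p₁ comes from the uncorrected chi-square test and p₂ from the t-test among resumers. It is compared with chi-square on 4 degrees of freedom (critical value 9.49). Simulated power is 78%, against 80% stated, so the planned figure reproduces. The chi-square component alone has about 52%.

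**What a subgroup already at level could do.** The share f is not in the article; 10, 20 and 30% are assumed. Suppose all of these patients resume in both arms, and the planned 0.50 v 0.75 applies to the rest. The rates become f + (1 − f) × 0.50 and f + (1 − f) × 0.75, and the difference is 25 × (1 − f) points.

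| f | Rates | Difference (points) | Chi-square power |
|---|---|---|---|
| 10% | 0.550 v 0.775 | 22.5 | about 45% |
| 20% | 0.600 v 0.800 | 20.0 | about 39% |
| 30% | 0.650 v 0.825 | 17.5 | about 34% |

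Combined power then depends on what is assumed about this subgroup:

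| Assumption for the subgroup | f = 10% | 20% | 30% |
|---|---|---|---|
| All resume; planned 15 v 12 weeks kept | 76% | 74% | 74% |
| 90% resume; 12 weeks, SD 4, in both arms | 65% | 53% | 42% |
| All resume; 8 weeks, SD 2, in both arms | 59% | 45% | 34% |

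The last row is an adverse corner. A mean of 8 with SD 2 puts week 6 at (6 − 8)/2 = −1 SD, so about 16% of the subgroup would be back in sport before the plan permits it.

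**Chance imbalance.** With f = 20% and 34 per arm, treating each arm's count as an independent binomial, the arms differ by 4 or more such patients with probability about 29%. Four of 34 is 11.8 percentage points of the arm. If these patients always resume and the others resume at 0.50, four extra in the control arm raise its rate by 0.118 × (1 − 0.50) = 5.9 points. Against 0.75 in the active arm the shift is 0.118 × (1 − 0.75) = 2.9 points.

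**The case against.** A reader might infer that these patients enter with the endpoint already met, or that dilution is established and the sample size is wrong. The article supports neither.

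- The study question is return to sport after debridement and microfracturing, not recovery of sport lost to the defect. Someone who played with pain until the operation still has to stop and return, and treatment could speed that. This stands in full.
- The share of such patients is unknown. They are symptomatic enough to be scheduled for surgery, so it may be small.
- The 50% resumption rate rests on the investigators' experience and may already include them. If 0.50 and 0.75 are the overall rates and 15 v 12 weeks holds throughout, power stays at about 78% whatever the share. No stated figure is shown to be wrong.
- If the treatment effect is the same in these patients, there is no dilution.
- Chance imbalance can arise in any unstratified predictor. Randomisation keeps the test valid on average, and AAS is in the baseline summary, so an imbalance could be seen.
- Covariates are often left to a statistical analysis plan. Here, however, the article itself says which variables enter the primary analysis. Asking that one more collected baseline variable be named there is a comment on what is written, not on what is absent.

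These points remove any claim of certain or large dilution. They do not remove the case for using a measured and probably strong predictor.

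**Conclusion.** The point holds as one about the analysis. Eligibility mixes patients with little or no preoperative deficit and patients with a large one. The deficit is collected, and it is used neither in stratification nor, as written, in the primary analysis. That it predicts both outcomes strongly is a judgement; the article gives no data on it.

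The effect on power is conditional. It ranges from almost none (74 to 76%, against 78%) to a fall to 59, 45 or 34% at shares of 10, 20 or 30%. The low end needs every such patient to resume early with no treatment effect, and the planning rates to exclude them.

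A reader might also conclude that entry should require a lost level. That does not follow. It would narrow the population, slow recruitment to a 68-patient trial and, if made part-way, mix two populations, all to cure a dilution that is not demonstrated.

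**What to change.** In Statistical methods, define the AAS deficit as pre-symptoms minus preoperative AAS. Name it as a prespecified covariate alongside the stratification variables in the primary analysis of both resumption and time to resumption. Report by arm the share of patients whose deficit is 0 or 1 point. Add a supportive analysis restricted to patients with a deficit of at least 2 points. Settle this before the allocation codes are broken. Leave eligibility unchanged.

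No new data are needed. The cost is one more covariate in a small trial that already plans to include three stratification variables, one of them a five-level center factor. The adjusted forms of the chi-square and t-test comparisons, already implied by including those variables, would carry this one too. The restricted analysis will be smaller and less precise, and should be read as support only.

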### Exclusion criteria

• Concomitant OD of the tibia

• Ankle osteoarthritis grade 2 or 3 [36]

• Ankle fracture < 6 months before scheduled arthroscopy

• Surgical treatment of the index ankle performed < 1 year before scheduled arthroscopy

• Concomitant painful or disabling disease of the lower limb

• Rheumatoid arthritis

• Pregnancy

• Implanted pacemaker

• Participation in concurrent trials

• Participation in previous trials < 1 year, in which the subject has been exposed to radiation (radiographs or CT)

• Patients who are unable to fill out questionnaires and cannot have them filled out

• No informed consent

### Device description

PEMFs are applied using a portable generator attached to the ankle (Figure 1). The coil in the active treatment device generates a peak magnetic field intensity of 1.5 mT, supplied by an electric pulse frequency of 75 Hz [37]. The sham devices do not differ from active devices in shape, color, weight, and in acoustic or visual signaling. Neither the active nor the sham device produces noise or sensation and they are entirely indistinguishable. The only difference is the generated magnetic field; the sham device produces a negligible peak of less than 0.05 mT, supplied by the minimal current necessary to power the device indicators.

